#### Headache frequency

the second primary outcome variable, is determined from the daily headache diary as the total number of headache hours during a 24-hour period. A second dimension of headache frequency is measured by the proportion of headache-free days experienced by a study participant (Figure 2). After receiving careful instruction, subjects record the presence and intensity of their headaches on an hourly basis. Subjects are also invited to comment on the nature of their headaches, the associated symptoms, and the suspected triggers.

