### Hypothesis

The trial is designed to test the hypothesis that, compared to those receiving usual care plus a treatment with low-strength static magnets (attention-control complementary therapy), subjects receiving usual medical care plus CST will demonstrate significant improvement in: quality-of-life as measured by the Headache Impact Test (HIT-6), a headache-specific quality-of-life measure; reduced frequency of migraine; and a perception of clinical benefit.

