#### Headache intensity

As noted, the headache diary captures headache frequency and intensity, as well as other information. Intensity is defined as mild, moderate, or severe. Guides to grading headache intensity are included with each diary. The total hours of moderate or severe headache during a 24-hour period will serve as the measure of intensity. Subjects are invited to comment on the nature of their headaches, the associated symptoms, and the suspected triggers.

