#### Analytic Strategy

Sample size and power calculations are based on the assumptions regarding the changes under treatment in two key measures of interest, namely, quality of life as measured by the Headache Impact Test (HIT) and headache frequency based on headache diary. Preliminary studies [41] have shown a mean HIT score of 63.7 with a standard deviation of 5.2 among migraine patients. Keeping the control values of HIT at this level, we estimate that with 45 subjects in each arm the study will have 80% power to detect a 3.5 points change in the HIT score. Based on our clinical experience we also estimate that, on average, migraine patients experience two headaches per week. With 45 patients per group, the study will have 80% power to detect a reduction in the headache frequency to one per week.

Regression modeling strategies will be used to test the primary hypothesis. A simple linear regression model with the HIT score at end of the study (16 weeks) controlling for HIT score at the baseline will be used to test for significant treatment effects. We will use repeated measures analysis on HIT measures to detect whether the change in HIT scores are significantly different between the two groups. Because of the correlated nature of the repeated measures, regression models using a generalized estimating equations (GEE) approach will be used to test the hypothesis of change. A significant time and treatment interaction will detect significant changes in the score. A similar analysis strategy using GEE methods will be used to analyze daily records of headache. All data analysis will be performed on an intent-to-treat basis. The GEE method assumes that missingness in data are completely at random. Under the missing at random assumption, it is possible to conduct analysis using multiple imputation procedures [42].

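### The stated 80% power for headache frequency is for headaches per week, but the primary outcome of that name is defined as headache hours per day and headache-free days

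*Protocol article*

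**What the plan says.** The article uses the term headache frequency in several places, and not for the same quantity.

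- **Hypothesis** (and the Abstract's Methods paragraph): one of the three expected effects is "reduced frequency of migraine". No time unit is given.
- **Eligibility:** headache frequency is a count, 5 to 15 per month.
- **Headache frequency**, under the primary outcome variables: the outcome "is determined from the daily headache diary as the total number of headache hours during a 24-hour period". The next sentence reads "A second dimension of headache frequency is measured by the proportion of headache-free days experienced by a study participant".
- **Table 3:** the diary measures have one row for frequency and a separate row for intensity and duration.
- **Analytic Strategy**, power: the starting point is that "on average, migraine patients experience two headaches per week", and then "With 45 patients per group, the study will have 80% power to detect a reduction in the headache frequency to one per week".
- **Analytic Strategy**, analysis: "A similar analysis strategy using GEE methods will be used to analyze daily records of headache". The response variable is not named.

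**The concern.** Hours of headache per day measure burden: how many attacks there are, multiplied by how long they last. Headaches per week measure how many attacks there are. A power statement for one says nothing about the other unless attack duration and its variability are brought in, and the article gives neither.

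Two things are at stake. First, a reader takes the 80% as the trial's power for its second primary outcome, when the power for hours per day or for headache-free days is unknown. Second, a treatment that shortens attacks without preventing any would lower the defined outcome and could be reported under the name of reduced frequency. The reverse can also happen: fewer but longer attacks could leave the hours unchanged. The Discussion says that the data will supply effect sizes for a larger, definitive trial, so the ambiguity would be carried into that trial's planning.

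**Working it through.** **Step 1. Can the 80% be reproduced for headaches per week?**

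Inputs from Analytic Strategy: control rate 2 per week, target rate 1 per week, so δ = 1 per week; n = 45 per arm; power 80%. Not given for this figure: SD, significance level, sidedness, counting window. I assume a two-sided 5% test. Without an SD the figure cannot be reproduced; it can only be solved backwards.

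Normal approximation: SD = δ / [√(2/n) × (z₀.₉₇₅ + z₀.₈₀)] = 1 / [√(2/45) × (1.960 + 0.842)] = 1 / (0.2108 × 2.802) = 1.69 per week.

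The exact two-sample t calculation (noncentral t) gives 1.67 per week. Power by the same method at other SDs:

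| SD (headaches/week) | Power, 45 per arm, δ = 1 |
|---|---|
| 1.0 | 99.7% |
| 1.25 | 96% |
| 1.5 | 88% |
| 1.67 | 80% |
| 2.0 | 65% |
| 2.5 | 47% |
| 3.0 | 35% |

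A count model gives a similar spread. Take rates of 2 and 1 per week observed for T weeks, with variance of the observed rate μ/T + kμ², and power = Φ(1/√[(v₁ + v₂)/45] − 1.96). For T = 8:

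- k = 0.5: v₁ = 2/8 + 0.5 × 4 = 2.25, v₂ = 1/8 + 0.5 = 0.625; power 97.7%.
- k = 1: v₁ = 4.25, v₂ = 1.125; power 82.5%.
- k = 2: v₁ = 8.25, v₂ = 2.125; power 54.9%.

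So 80% is attainable for headaches per week under moderate between-subject variation. It can be neither confirmed nor refuted from the article.

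**Step 2. Does the 80% carry over to hours per day?**

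The article gives no mean, SD or target difference for hours per day, so no single power figure exists. As an illustration only, assume that mean hours are also halved. Then δ is half the control mean, and the Step 1 calculation rescales: 80% power needs SD ≤ 0.5 × 1.67 ≈ 0.84 times the control mean. Power for other ratios of SD to control mean:

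| SD / control mean | Power |
|---|---|
| 0.75 | 88% |
| 1.0 | 65% |
| 1.25 | 47% |
| 1.5 | 35% |

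Nothing in the article says where in this range the trial sits. The same holds for headache-free days: no SD or target difference is given.

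**Step 3. Can hours and frequency move apart?**

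Illustration with assumed attack durations, each attack falling within one calendar day unless stated:

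| Pattern | Attacks/week | Hours/day | Headache-free days |
|---|---|---|---|
| Two 12-hour attacks | 2 | 24/7 = 3.43 | 5/7 |
| Two 6-hour attacks | 2 | 12/7 = 1.71 | 5/7 |
| One 24-hour attack | 1 | 24/7 = 3.43 | 6/7 (5/7 if it spans two days) |

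From the first row to the second, hours halve with no change in the number of attacks. From the first to the third, attacks halve with no change in hours.

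**The case against.** The strongest reply is that the primary outcome already contains a genuine frequency measure. The proportion of headache-free days stands directly after the hours definition, and in the second pattern of Step 3 it would show that attacks had become shorter but not fewer. This stands, and it reduces the risk of misreading. It does not remove the mismatch: headache-free days are only a second dimension, neither dimension is named as decisive, and a headache day is not the same unit as a headache.

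It can also be said that a weekly count could be derived from the daily records that the GEE analysis will use. That is true, so the text does not support saying that headaches per week will not be analysed. It supports only that no such count is defined as an outcome.

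The missing SD and significance level are details that a condensed article may leave to the full protocol, and they are not the point here.

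A reader might go further and infer that the 80% is wrong even for headaches per week, because a variable confined to 5–15 per month has an SD of at most 5 per month (roughly 1.15 to 1.25 per week), which would give 96% or more. The article does not support that. The window limits frequency at entry, not counts under treatment; the diary check in Baseline Period sets a minimum of 5 migraines and states no ceiling; and Step 1 shows that ordinary overdispersion gives about 80%. If the SD were that small, the stated power would in any case be conservative.

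A reader might also object that the intensity outcome, "The total hours of moderate or severe headache during a 24-hour period will serve as the measure of intensity", is a subset of the same hours. A secondary outcome may overlap with a primary one, and this is not a fault.

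Finally, the first aim is feasibility. That lowers the stakes, but the article states a hypothesis to be tested and claims power for it.

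**Conclusion.** The point holds in a limited form. The article fixes two incompatible meanings for one named primary outcome: hours per day (with headache-free days) in its definition, and headaches per week in its power statement. The 80% therefore does not apply to the outcome as defined, and power for either defined dimension cannot be derived from the article. Under the illustrative assumption that hours are halved, it runs from 88% to 35% as the SD goes from 0.75 to 1.5 times the control mean.

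For headaches per week, the 80% is unverified but not shown to be wrong. It corresponds to an SD of about 1.67 per week, assuming a two-sided 5% test with 45 per arm. A change in headache hours alone should not be reported as reduced frequency. The mismatch itself is read directly from the text and needs no assumption; the power figures rest on the assumptions stated with them.

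**What to change.** Make a documented amendment before unblinding that uses one definition of frequency in the hypothesis, outcome, power and analysis text.

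1. **Preferred.** Name the day-based measure as the frequency primary: headache days per 28 days, which is 28 × (1 − proportion of headache-free days). Label headache hours as a burden or duration outcome.
2. Replace the sentence about two headaches per week falling to one with the power, or the detectable difference, for headache days with 45 per arm. Take the SD from the 8-week baseline diaries, pooled and without reference to arm. Show a range above that SD, because baseline diaries come from a sample selected on headache frequency and the SD at follow-up may be larger.
3. Name the chosen variable as the response in the GEE sentence.
4. **If hours stay primary,** rename the outcome and the matching part of the hypothesis as headache burden, and withdraw the 80% statement or recompute it for hours per day.

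Cost: no new data, since the diaries already record headache by the hour. But recruitment is under way and some study staff may learn treatment assignments while reviewing diaries (Masking section). This is therefore a change to a primary outcome during the trial, to be dated, justified and decided without sight of outcome data by arm. The stated detectable effect will also change.

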**Figure 2 F2:**
[figure not shown]
**On-line Daily Headache Diary of the Clinical Feasibility Trial of Craniosacral Therapy (CST), 2006–2008 Legend: Subjects had the option of filling out the diary on paper or on line.** Detailed instructions were provided at the time of enrollment.

#### Self-perceived benefit

of the intervention, one aspect of Specific Aim 3, is measured at the end of the 8-week treatment period. Subjects rate the perceived benefit of the therapy on a five point scale ranging from "greatly worsened my clinical condition" to "greatly improved my clinical condition". In addition, they assess the therapy as "more harmful than helpful", "neither harmful nor helpful", or "more helpful than harmful".

#### Secondary outcome variables

Secondary outcome variables include the following: headache intensity, headache-associated symptoms, medication used, cost of medication, health care utilization, change in general health status, study credibility, degree of headache related disability (MIDAS), and satisfaction with care. These are discussed below.

#### Headache intensity

As noted, the headache diary captures headache frequency and intensity, as well as other information. Intensity is defined as mild, moderate, or severe. Guides to grading headache intensity are included with each diary. The total hours of moderate or severe headache during a 24-hour period will serve as the measure of intensity. Subjects are invited to comment on the nature of their headaches, the associated symptoms, and the suspected triggers.

#### Headache-associated healthcare utilization

The diary also captures medication use and visits with a health care provider. (Figure 2).

#### Functional status and general health-related quality of life

The Medical Outcomes Study Short Form (SF-36) is a widely-used functional status instrument that assesses eight different health domains: physical functioning; bodily pain; role limitations due to physical problems; role limitations due to emotional problems; general mental health; social functioning; vitality; and general health perceptions [32]. A daily measure of well-being is included in the daily headache diary.

#### Headache-related disability: MIDAS

Disability, defined as the consequences of illness on ability to work and function, is measured using the migraine disability assessment score (MIDAS). Derived from the Headache Impact Test, MIDAS is a 7-item questionnaire that assesses the number of days during the previous three months that respondents missed work or school, experienced decreased productivity at work or home, or missed social engagements because of headaches. Test-retest reliability is acceptable, with Spearman's correlation coefficient ranging from 0.67 to 0.73. Cronbach's alpha is 0.83 [33,34].

#### Control variables

Control variables include socio-demographic and clinical characteristics, as well as evaluation of subject bias and protocol variability. These are described below.

#### Socio-demographic and clinical characteristics

Age, gender, ethnicity, religion, occupation, employment status, level of education, income, type of medical insurance, date of onset of migraine, history of use of CST, and presence of other medical conditions and diagnoses are collected at the time of the baseline interview. The medical history and physical exam performed by the PI are part of this data set. Subject weight, height, and vital signs are measured at the baseline visit.

### Evaluation of Subject Bias and Protocol Variability

#### Credibility and Expectation of Benefit

Subject credibility and expectations are assessed using an instrument adapted from a validated scale developed by Borkovec and Nau [35,36]. The instrument is administered just before the second visit. Data analysis will demonstrate whether subjects in the two groups have similar or different expectations of benefit. It has been shown that high expectations of treatment are closely related to better outcomes [37,38].

#### Quality control

Videotapes of the first, third, fifth, and seventh treatment sessions are used to provide feedback to the therapist to ensure standardization of the CST and LSSM treatment protocols as well as to identify any differences in therapist-subject behavioral interactions between the CST and LSSM treatments and thus control for interactional bias. Noldus 'Observer' Video-Pro System programmable software is used to code and analyze the selected videotaped sessions and quantitatively assess specific therapist and subject behaviors [39,40].

#### Adverse events

Reports of adverse events are obtained from subjects at each treatment session, from self reports recorded in the headache diaries or by direct contact with study staff. Adverse events are investigated by the study neurologist and are reported both to the UNC Institutional Review Board and the National Institutes of Health.

#### Analytic Strategy

Sample size and power calculations are based on the assumptions regarding the changes under treatment in two key measures of interest, namely, quality of life as measured by the Headache Impact Test (HIT) and headache frequency based on headache diary. Preliminary studies [41] have shown a mean HIT score of 63.7 with a standard deviation of 5.2 among migraine patients. Keeping the control values of HIT at this level, we estimate that with 45 subjects in each arm the study will have 80% power to detect a 3.5 points change in the HIT score. Based on our clinical experience we also estimate that, on average, migraine patients experience two headaches per week. With 45 patients per group, the study will have 80% power to detect a reduction in the headache frequency to one per week.

Regression modeling strategies will be used to test the primary hypothesis. A simple linear regression model with the HIT score at end of the study (16 weeks) controlling for HIT score at the baseline will be used to test for significant treatment effects. We will use repeated measures analysis on HIT measures to detect whether the change in HIT scores are significantly different between the two groups. Because of the correlated nature of the repeated measures, regression models using a generalized estimating equations (GEE) approach will be used to test the hypothesis of change. A significant time and treatment interaction will detect significant changes in the score. A similar analysis strategy using GEE methods will be used to analyze daily records of headache. All data analysis will be performed on an intent-to-treat basis. The GEE method assumes that missingness in data are completely at random. Under the missing at random assumption, it is possible to conduct analysis using multiple imputation procedures [42].

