**Methods:**

The trial is designed to test the hypothesis that, compared to those receiving usual care plus a treatment with low-strength static magnets (attention-control complementary therapy), subjects receiving usual medical care plus CST will demonstrate significant improvement in: quality-of-life as measured by the Headache Impact Test (HIT-6); reduced frequency of migraine; and a perception of clinical benefit. Criteria for inclusion are either gender, age > 11, English or Spanish speaking, meeting the International Classification of Headache Disorders (ICHD) criteria for migraine with or without aura, a headache frequency of 5 to 15 per month over at least two years. After an 8 week baseline phase, eligible subjects are randomized to either CST or an attention control intervention, low strength static magnets (LSSM). To evaluate possible therapist bias, videotaped encounters are analyzed to assess for any systematic group differences in interactions with subjects.

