### Randomization

Subjects are randomized to one of the two treatment arms using a concealed allocation protocol. At the subject's first treatment visit, the study therapist performs a brief intake interview and then opens an opaque, sequentially numbered envelope that identifies which treatment group has been randomly selected for this subject. The randomization scheme uses a permuted block method to generate the intervention assignment sequence being implemented at the treatment location to assure that the randomization balance is maintained throughout enrollment [24].

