### Outcome measures and study instruments

#### Primary outcome variables

The primary outcome variables assessed for this study include headache-specific quality-of-life, frequency of headache and self perceived benefit of the intervention (Table 3 describes measurement points for these variables). Detailed descriptions of these variables follow:

**Table 3 T3:** Summary of Measures and Timing of Administration for Clinical Feasibility Trial of Craniosacral Therapy, 2006–2008

	**Week 0**	**Weeks 1 to 8**	**Weeks 8 to 16**	**Weeks 16 to 20**
**Variable or Instrument**	**Baseline Assessments**	**Baseline with Usual Care**	**Usual Care plus CST or LSSM**	**Post-treatment Assessments**

Demographic/Clinical Data	Week 0			
	ICHD* Diagnosis	Week 0		
Functional status – MOS SF-36	Week 0			Week 20
Expectation of benefit/Credibility †			(post 1^st^ treatment)	
Headache QOL – HIT-6 §	Week 0	Week 8		Week 16
Headache Diary: Frequency		Daily	Daily	
Perceived clinical change		Week 8		Week 16
Headache disability – MIDAS #	Week 0			Week 20
Headache Diary: Intensity and Duration		Daily	Daily	Daily
Headache Diary: Medication Use/Cost		Daily	Daily	Daily
Headache Diary: Health care visits		Daily	Daily	Daily
Satisfaction with care	Week 0	Week 8		Weeks 16, 20
Blood pressure and heart rate	Week 0		Weekly	
Therapist – Subject Interaction Analysis Videotaping Encounters**			Weeks 9,11, 13 & 15	

* International Classification of Headache Disorders, defined by expert members of the International Headache Society

† Based on a measure developed by Borkovec and Nau to measure credibility of psychological interventions [38,39].

§ Headache Impact Test was developed to measure headache-related quality of life [33].

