#### Headache Impact Test (HIT-6)

Headache-specific quality of life is measured as the change in headache-related disability at 8 weeks after randomization as assessed by the HIT-6. The HIT-6 is a validated questionnaire designed "to measure the impact headaches have on a person's ability to function on the job, at school, at home, and in social situations" [30]. It has good internal reliability [31]. The scale consists of six items that cover various content areas relevant to headache-related disability: pain, social functioning, role functioning, vitality, cognitive functioning, and psychological distress. A decrease of 2.3 HIT points (95% CI, 0.3 to 4.3) over six weeks among patients with chronic headache corresponds to a "somewhat better" self-reported rating on a global clinical change scale [31].

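### The HIT-6 regression adjusts for one unspecified baseline score although two readings precede randomisation: a missed gain in precision, not an error

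*Protocol article*

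**What the plan says.** **Model.** The Analytic Strategy section tests the HIT-6 hypothesis with "A simple linear regression model with the HIT score at end of the study (16 weeks) controlling for HIT score at the baseline". The score is singular and its week is not given. The next sentence adds a second analysis: "We will use repeated measures analysis on HIT measures to detect whether the change in HIT scores are significantly different between the two groups". This is a GEE model judged by the time-by-treatment interaction. The section does not rank the two.

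**Measurement times.** Table 3 lists "Headache QOL – HIT-6 § Week 0 Week 8 Week 16". Week 0 stands in the column for baseline assessments. Week 8 stands in the column for the baseline period under usual care. Both headings therefore carry the word baseline.

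**Randomisation.** The Abstract (Methods) states: "After an 8 week baseline phase, eligible subjects are randomized to either CST or an attention control intervention". The Randomization section places allocation at the start of treatment: "At the subject's first treatment visit, the study therapist performs a brief intake interview and then opens an opaque, sequentially numbered envelope". Table 3 dates the videotaped sessions to weeks 9, 11, 13 and 15, and the Quality control section says these are the first, third, fifth and seventh sessions. The first treatment visit therefore falls in week 9, after the week-8 reading.

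**Outcome.** The HIT-6 section defines the outcome as "the change in headache-related disability at 8 weeks after randomization as assessed by the HIT-6".

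**The concern.** Two HIT-6 scores are scheduled on every subject before allocation, and the stated regression uses one. A single score is a noisier guide to a subject's usual level than two, so the second can remove residual variance from the treatment comparison without any further data collection.

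The wording also leaves open which score is meant. Read literally against Table 3, an analyst could adjust for week 0 alone, a score about 8 weeks older than randomisation, and ignore the nearer one.

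At stake is the width of the confidence interval for a primary outcome with 45 subjects per arm. This matters because the Discussion says the analyses will supply effect sizes for a larger, definitive trial.

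**Working it through.** **Inputs from the protocol.** SD 5.2 ("Preliminary studies [41] have shown a mean HIT score of 63.7 with a standard deviation of 5.2 among migraine patients"), 45 per arm, target difference 3.5 points, stated power 80%.

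**Assumptions.** Two-sided alpha 0.05; equal SD at each visit; complete data. No HIT-6 correlation is given, so a range is used.

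**1. The plan's own figure.** Unadjusted SE = 5.2 × √(2/45) = 1.096. Power at 3.5 points = Φ(3.5/1.096 − 1.96) = 89%, against 80% stated. The stated figure is lower than its inputs give. An unstated dropout allowance of 20% on 36 per arm (36/0.8 = 45) would explain it. That is a separate matter; here it shows only that the target is adequately powered before any baseline adjustment.

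**2. Equal correlation r among weeks 0, 8 and 16.** Residual variance, as a fraction of the raw variance:
- one baseline: 1 − r²
- both baselines: 1 − 2r²/(1 + r)

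| r | One | Both | Ratio | SE, one → both | Power at 3.5, one → both |
|---|---|---|---|---|---|
| 0.3 | 0.910 | 0.862 | 0.947 | 1.046 → 1.018 | 91.7% → 93.1% |
| 0.5 | 0.750 | 0.667 | 0.889 | 0.949 → 0.895 | 95.8% → 97.4% |
| 0.6 | 0.640 | 0.550 | 0.859 | 0.877 → 0.813 | 97.9% → 99.0% |
| 0.7 | 0.510 | 0.424 | 0.830 | 0.783 → 0.713 | 99.4% → 99.8% |
| 0.8 | 0.360 | 0.289 | 0.802 | 0.658 → 0.589 | about 100% for both |

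The variance falls by 5% to 20%. At r = 0.6 the 95% half-width falls from 1.96 × 0.877 = 1.72 to 1.96 × 0.813 = 1.59 points. The gain equals 45/0.889 = 50.6 subjects per arm at r = 0.5 and 45/0.802 = 56.1 at r = 0.8.

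**3. Decaying correlation, first-order autoregressive** (r per 8 weeks, r² over 16 weeks). Given week 8, week 0 carries no further information, so both readings leave 1 − r².
- Week 8 already used: ratio 1, no gain.
- Week 0 alone used: residual variance is 1 − r⁴. The ratio (1 − r²)/(1 − r⁴) = 1/(1 + r²) is 0.80, 0.735, 0.671 and 0.610 at r = 0.5, 0.6, 0.7 and 0.8. Bringing in week 8 therefore removes 20% to 39%.

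**4. Intermediate decay** (week 0 to week 16 correlation halfway between r and r², r = 0.5 to 0.8). Both readings against week 8 alone: variance ratio 0.972 to 0.951, that is, an SE 1% to 3% lower. Against week 0 alone: variance ratio 0.848 to 0.711.

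**5. The plain mean of the two scores.** Under the autoregressive pattern its residual variance is 1 − r²(1 + r)/2, against 1 − r² for week 8 alone. At r = 0.5 this is 0.8125/0.75 = 1.083; at r = 0.8 it is 0.424/0.36 = 1.178. The mean can therefore be 8% to 18% worse in variance than week 8 alone.

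**6. Cost of the extra covariate.** Residual degrees of freedom go from 90 − 3 = 87 to 90 − 4 = 86. With p random baseline covariates, chance imbalance inflates the variance by about (90 − 3)/(90 − p − 3): 87/86 for one and 87/85 for two. A second covariate that adds nothing therefore costs about 86/85 − 1 = 1.2% of variance, or 0.6% of the SE.

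**The case against.** **No error is shown.** Regressing the final score on one baseline score is standard and valid. It brings no bias and no inflation of type I error, and section 1 of the working shows ample power at 3.5 points. All of this stands, and it limits the point to efficiency.

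**The word baseline may be settled elsewhere.** A condensed article can leave the definition to the full protocol, and the outcome definition, change at 8 weeks after randomisation, points to week 8. This also stands. A reader might infer that the plan adjusts for week 0 and discards week 8, and so take 20% to 39% as the loss. The text permits that reading but does not state it, and week 8 is the more natural one.

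**The GEE may already use all three readings.** This stands in part. It means that one cannot say the data go unused, or call the regression the primary estimate. But the GEE need not recover the gain. With linear time and complete data at weeks 0, 8 and 16, under an independence or exchangeable working correlation, the slope weights are −1, 0, +1, so week 8 gets no weight. With categorical time, each interaction is a change from one reference visit.

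**The 2.3-point figure.** A reader might judge power at 2.3 points, where the second reading matters more. The HIT-6 section gives 2.3 as a change in patients' own scores that corresponds to a self-rating of somewhat better. It is not the between-arm target, so it does not show that the trial is short of power.

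**Conclusion.** The point holds as a missed gain in precision. Two pre-randomisation HIT-6 readings are scheduled, and the regression names one without saying which.

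If week 8 is the intended covariate, adding week 0 lowers the residual variance by 0% (autoregressive decay) to about 20% (equal correlation 0.8), or up to about 10% of the SE. If week 0 alone is intended, the reduction is 20% to 39% under autoregressive decay and 15% to 29% under the intermediate pattern, for r from 0.5 to 0.8. Every one of these figures rests on assumed correlations and equal SDs.

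A flat statement that the planned estimate is less precise than it could be goes too far, because in one plausible case nothing is gained. The case for acting is that the possible gain is useful for estimating an effect size, while the possible loss is about 1% of variance.

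**What to change.** Replace the covariate wording in the Analytic Strategy section with a model such as: week-16 HIT-6 regressed on treatment, week-8 HIT-6 and week-0 HIT-6, the two earlier scores entered as separate covariates, in all randomised subjects. Do not substitute their mean, which can do worse than week 8 alone. The same sentence settles which reading counts as baseline.

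The change should be recorded before treatment codes are released to the biostatistician, whom the Masking section describes as unaware of assignment.

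Cost: one sentence, no new data and one extra model degree of freedom (86 residual instead of 87 with 90 subjects).
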